**Other measures**					
Self-rated work ability	WAI [20, 21]	Continuous	X		
Self-evaluation of functional capacity	M-SFS [30, 31]	Continuous		X	
Outpatient visits to physicians	Own development	Continuous	X		
Use of outpatient therapy	Own development	Continuous			X
Use of rehabilitation	FIMA [32]	Binary			X
Job title	Own development	Nominal	X		X
Working hours	Own development	Ordinal	X		
Temporary work	Own development	Nominal	X		
Fixed-term job contracts	Own development	Nominal	X		
Shift work	Own development	Nominal	X		
Size of company	Own development	Nominal	X		
Sociodemographic data	Own development	Nominal/continuous	X		
Dose delivered: initial consultation	Computerized sheet (own development)	Binary/continuous		X	
Dose delivered: two-day diagnostics	Computerized sheet (own development)	Binary/continuous		X	
Dose delivered: follow-up consultations	Computerized sheet (own development)	Binary/continuous			X
Self-evaluation of functional capacity	Own development	Continuous		X	
Action skills	Own development	Continuous		X	
Subjective goal achievement	Own development	Continuous			X
Content of intervention	Own development	Continuous		X	X
Rating of intervention components	Own development	Continuous			X

*WAS* Work Ability Score, *COPSOQ* Copenhagen Psychosocial Questionnaire, *PHQ* Patient Health Questionnaire, *RMQ* Roland and Morris Disability Questionnaire, *BSA-F* Bewegungs- und Sportaktivität Fragebogen, *FEBA* Fragebogen zur subjektiven Einschätzung der Belastungen am Arbeitsplatz, *WAI* Work Ability Index, *M-SFS* Modified Spinal Function Sort, *FIMA* Fragebogen zur Inanspruchnahme medizinischer und nicht-medizinischer Versorgungsleistungen im Alter

#### Primary outcome

Our primary outcome is self-rated work ability using the single-item Work Ability Score (WAS), which is the first item of the Work Ability Index (WAI) and measures current compared with lifetime best work ability [20, 21]. The score ranges from 0 (completely unable to work) to 10 (work ability at its best). Higher scores indicate better self-rated work ability. The WAS is closely correlated with the entire Work Ability Index score [21], and predicts work disability and health-related early retirement [33–35]. The WAS is assessed during the initial consultation with the occupational health physician, and at the six-month follow-up, and also at the end of the two-day diagnostics.

#### Secondary outcomes

Our secondary outcomes with regard to health, physical functioning, mental health and employment are assessed in the initial consultation and at six-month follow-up, and also to some extent at the end of the two-day diagnostics.

##### General health

General health will be assessed with one item from the Copenhagen Psychosocial Questionnaire using an 11-point scale (0 ‘worst imaginable health state’ to 10 ‘best imaginable health state’) [22, 23]. General health is also assessed at the end of the two-day diagnostics.

##### Depression and anxiety

The two-item versions of both the depression module (PHQ-2) and the anxiety module (GAD-2) of the Patient Health Questionnaire (PHQ-4) will be used to assess depression and anxiety [24, 25]. All items are measured on a four-point scale (0 = not at all, 1 = several days, 2 = more than half of the days, 3 = nearly all days). Total scores for depression and anxiety range from zero to six points. We will also determine binary outcomes by categorizing values of > 2 as clinically relevant depressive or anxiety disorder. Information about depression and anxiety will also be collected at the end of the two-day diagnostics.

##### Physical functioning

Physical functioning is assessed using the Roland and Morris Disability Questionnaire (RMQ) [26, 27]. The RMQ consists of 24 items related to impairments with regard to activities of daily living. Participants are asked to state the items which describe their impairments. Each item is coded with 0 and 1, resulting in a total score of 0 to 24 points. A higher score indicates higher impairment and disability.

##### Physical activity 

Physical activity will be assessed using the German Physical Activity, Exercise, and Sport Questionnaire (Bewegungs- und Sportaktivität Fragebogen, BSA-F) [28]. We will assess the number of different exercise activities undertaken during the last four weeks and the frequency and duration in minutes of each activity. Frequency and duration are multiplied for each mention of activity. The products are summed to obtain a total physical activity index and divided by four to get the unit minutes per week.

##### Employment

We will assess employment state (employed vs. unemployed) to describe work participation. We will also ask for the number of weeks of sickness absence (current state and duration in the past six months).

##### Work stress and work environment 

Physical job demands will be measured using the questionnaire on job demands (Fragebogen zur subjektiven Einschätzung der Belastungen am Arbeitsplatz, FEBA) [29]. The FEBA consists of five 4-point items that yield a total score ranging from 0 to 15 points. Higher values indicating higher levels of job demands.

Psychological job demands (six items), job insecurity (two items), support by supervisor and colleagues (two items), atmosphere at work (one item), and overall job satisfaction (one item) will be assessed using the short version of the Copenhagen Psychosocial Questionnaire (COPSOQ) [22, 23]. Total scores for these variables range from 0 to 100 points. Workplace bullying will be assessed with a single 5-point item. The total score ranges from 0 to 100 points.

#### Other measures

Data for other variables will be collected at baseline in order to provide a description of the study sample at the end of the two-day diagnostics, to obtain the received therapy dose, and at the six-month follow-up to obtain an overall rating of interventions elements and information on healthcare utilization during the intervention and waiting period (Table 2).

##### Work Ability Index

Work ability is assessed using the German version of the WAI questionnaire [20, 21]. The total WAI score ranges from 7 to 49 points. Higher scores indicate better work ability. Levels of work ability can be categorized as poor (7–27 points), moderate (28–36 points), good (37–43 points), and excellent (44–49 points).

##### Healthcare utilization

Outpatient visits to physicians will be assessed at baseline as the number of visits in the last 12 months. Hospitalization within the last 12 months will be captured at baseline as the number of visits in the last 12 months.

Outpatient therapy (e.g., physiotherapy, psychotherapy or stress management training) will be assessed at six-month follow-up as the number of therapy units in the six months since the initial consultation. The use of in- and outpatient rehabilitation in the last six months will be assessed at six-month follow-up using an adapted item from the German Questionnaire for Health-Related Resource Use in an Elderly Population (Fragebogen zur Inanspruchnahme medizinischer und nicht-medizinischer Versorgungsleistungen im Alter, FIMA) [32].

##### Socio-demographic and work-related data 

We will ask participants for socio-demographic data (age, gender, native language, educational level, partnership and children), and work-related data (job position, job title, weekly working hours, fixed-term job contracts, temporary work, size of company and shift work).

##### Self-evaluation of functional capacity

The self-evaluation of functional capacity will be assessed using the Modified Spinal Function Sort (M-SFS) [30, 31]. The M-SFS measures self-efficacy in performing work-related demands and contains 20 drawings with simple written descriptions of the demands. Participants will rate their self-efficacy for each demand on a 5-point scale including 4 (able), 3, 2 or 1 point (restricted) or 0 points (unable). Items are summed to obtain a total score ranging from 0 to 80. Higher scores indicate greater self-efficacy to perform the tasks.

##### Delivered dose

Occupational health physicians document the intervention components (i.e., initial and follow-up consultations) in a standardized manner using computerized sheets. The study coordinators document the two-day comprehensive diagnostics (i.e. duration of diagnostic and therapeutic elements) in a standardized manner using computerized sheets.

##### Received dose

The participants will rate five items on the received content of the initial consultation, six items on the received content of the two-day diagnostics, five items on action skills, seven items on the consistency of the intervention (e.g., workplace orientation, comprehensiveness) and five items on the subjective goal achievement. The ratings of these items use a 4-point scale from 0 (do not agree) to 3 (completely agree). Finally, we will also ask the participants to rate the different components of our intervention strategy (i.e., initial consultation, two-day diagnostics and follow-up consultations), with grades from 1 (very good) to 5 (insufficient).

### Participant timeline

Table 3 shows the full schedule of enrollment, interventions and assessments.

**Table 3 Tab3:** Schedule of enrollment, intervention, and assessments

*Timepoint*	*Initial consultation*	*Randomization*	*Two-day diagnostics*	*Follow-up consultations*	*Six months after initial consultation*	*Two-day diagnostics*	*Follow-up consultations*
**Enrollment**							
Screening and information letter	X						
Randomization		X					
**Interventions**							
Intervention group	X		X	X			
Waiting-list control group	X					X	X
**Assessments**							
Baseline questionnaire	X						
Questionnaire at the end of the two-day diagnostics			X			X	
Six-month follow-up questionnaire					X		
Computerized documentation by occupational health physicians	Continuously						
Participant interviews				X			X

### Sample size

A total number of cases of 128 persons, (64 persons per intervention arm) is necessary (two-sided type I error rate: 5%, power: 80%) in order to ensure a difference of 1 point on the Work Ability Score (standard deviation = 2). The standard deviation was estimated according to comparable studies [21, 33–35]. Although we will use multiple imputations to perform an intention-to-treat analysis, we will increase the sample size to compensate for the potential loss of participants during our follow-up assessments. This ensures sufficient power even if only complete cases are analyzed. Assuming a response rate of 60% after six months, we will recruit 210 patients in total: 105 patients per group.

Of the 210 persons recruited, 18 participants (nine from each of the intervention and control group) will be recruited to take part in interviews.

### Recruitment

Potential participants for the intervention will be identified in the cooperating companies by the responsible occupational health physician. Those employed in the cooperating companies for at least six months and who have health impairments and limited work ability are included. The proposal to include these employees in the study can come from various sources: the manager, the occupational health management, works council, occupational health physician or the employees themselves. Participation is voluntary for the employees. The occupational health physician is responsible for inclusion in the project.

The occupational health physician will distribute the study documents as information for the employees in the initial interview. An information letter will detail the content and objectives of the study, as well as the employee’s personal rights regarding the handling of personal data. Participants will give their informed consent and complete the baseline questionnaire. If the follow-up questionnaire is not returned, a questionnaire will be sent again, with a reminder to all participants after three weeks.

The study coordinators will carry out recruitment for the interviews in the rehabilitation centers. Informed consent forms will be handed out at the end of the two-day diagnostics. Participants will also receive a contact form that they can complete if they agree to participate in interviews. The completed contact form will be sealed by participants in a prepaid envelope addressed to the University of Lübeck. After receiving the contact form, the University of Lübeck will contact the participants and arrange an interview date.

### Allocation

A separate randomization sequence will be created by the principal investigator (MB) for each rehabilitation center using Stata 16.0. Blocks of four and six will be combined in the computer-generated randomization lists, in order to guarantee balanced case numbers, even if the lists cannot be processed completely. The randomization envelopes are consecutively numbered and non-transparently sealed.

Participants will be informed that there are two different study groups (intervention and control group), and that allocation to the two groups is randomized, during the initial consultation with the occupational health physician. After a participant has given their consent, the occupational health physician will contact the study coordinator and register them for the two-day diagnostics. The study coordinator will then open the randomization letter and communicate the group assignment to the occupational health physician and the participant by telephone, and coordinate the start of the two-day diagnostics.

### Blinding

Occupational health physicians conduct the initial consultation without knowing the group assignment. After randomized allocation no one will be blinded during or after the trial, as the realized intervention will be recognizable for all stakeholders. The principal investigator and data analysts will be aware of group assignments when analyzing the data.

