### Data management

A comprehensive data protection concept has been developed with the data protection officer from German Pension Insurance North which clarifies the data processing, the rights of participants, and technical and organizational measures in order to ensure the secure and confidential collection, processing, and storage of data. Data from the questionnaires will be entered, reviewed and exported to statistical software packages for further analysis. Data input and data verification will be performed by trained research assistants.

Recordings from the interviews will be transcribed by trained assistants at the University of Lübeck. Names and places will be removed during the transcription process.

Access to the data is limited to the first and last author and research assistants on the research team, and data management is performed by these authors.

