### Statistical methods

Linear mixed models will be used for continuous outcomes and logistic mixed models for binary outcomes. We will include a random intercept to consider varying outcomes in different rehabilitation centers.

Baseline scores of outcomes will be included as covariates. In order to perform an intention-to-treat analysis, we will use multiple imputation to augment incomplete responses to the six-month follow-up questionnaires. Exploratory moderator analyses examine whether estimates differ for sex, job position, size of company, and the rehabilitation center [36].

We will not perform interim analyses or specify a stopping rule. Statistical tests will be regarded as significant if the two-sided *p*-value is less than 0.05. An up-to-date version of Stata (StataCorp, College Station, Texas, USA) will be used to conduct analyses.

The interviews will be transcribed and analyzed using qualitative content analysis.

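### Principal investigator and analysts are to see group assignments at analysis, for a reason that does not cover an analyst working on coded data

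*Protocol article*

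**What the plan says.** The protocol article, Blinding, gives one ground for the open design: "After randomized allocation no one will be blinded during or after the trial, as the realized intervention will be recognizable for all stakeholders". The next sentence carries this into the analysis: "The principal investigator and data analysts will be aware of group assignments when analyzing the data". It adds no separate reason for analysts.

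Three other sections bear on the point.

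- **Allocation:** "A separate randomization sequence will be created by the principal investigator", one for each rehabilitation center. Numbered, opaque, sealed envelopes are opened by the study coordinator after consent.
- **Data management:** "Access to the data is limited to the first and last author and research assistants on the research team, and data management is performed by" those same two authors. Trained research assistants enter and verify the questionnaire data.
- **Statistical methods:** "we will use multiple imputation to augment incomplete responses to the six-month follow-up questionnaires". The section also fixes linear mixed models for continuous outcomes, a random intercept for center, adjustment for the baseline score, a two-sided 0.05 threshold, no interim analyses and a short list of exploratory moderators.

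Under Sample size the expected non-response is explicit: "Assuming a response rate of 60% after six months, we will recruit 210 patients in total: 105 patients per group".

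No section of the article mentions coded group labels, a masked analysis or an independent analyst.

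**The concern.** Recognisability explains why the people who deliver or receive the service cannot be blinded. It does not explain why someone fitting a model to questionnaire scores must know which arm is which. The plan therefore gives up a safeguard on grounds that do not reach the people concerned.

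This matters more here than in many trials. The primary outcome is a single self-rated item, participants know their group, and a large share of primary values is expected to be missing. Any judgement left at analysis, for example in building the imputation model, would be exercised with the arms visible. The principal investigator, who also produces the allocation lists, is among those unmasked.

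**Working it through.** **Inputs (Sample size section).** Difference of 1 point on the Work Ability Score (WAS), SD 2, "two-sided type I error rate: 5%, power: 80"%, 64 per arm evaluable, 60% response, 210 recruited.

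**Step 1: reproduce the plan's figures.** The standardised difference is 1/2 = 0.5. A two-sample t-test needs 63.77 per arm, so 64 per arm and 128 in total, with power 0.801. This matches the plan. Allowing for 60% response gives 128/0.60 = 213.3, so 214 against the stated 210, a gap of under 3%. The sample size is not in dispute.

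**Step 2: how many primary values would be imputed.**
- Observed: 210 × 0.60 = 126, or 63 per arm if response is equal in the two arms (t-test power 0.795).
- Missing: 210 − 126 = 84, which is 40%.

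**Step 3: how much the estimate depends on the imputed values.** With 40% of each arm imputed, a shift of d points in the imputed values of one arm relative to the other moves the group difference by 0.40 × d. The documents give no value for d, so the range below is an assumption.

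| Assumed d (points) | Movement in estimate (points) |
|---|---|
| 0.25 | 0.10 |
| 0.5 | 0.20 |
| 1.0 | 0.40 |

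For scale, the unadjusted standard error with 63 per arm is 2 × √(2/63) = 0.356, and the target difference is 1 point. The table describes sensitivity to imputation in general and would be the same with masked analysts. It shows why the stage deserves protection. It does not measure the effect of knowing the arms.

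**Step 4: does the primary analysis need arm-revealing data?** Compare Statistical methods with Tables 1 to 3.

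- *Needed for the primary model:* baseline WAS, six-month WAS and center. All exist in both arms. The planned moderators (sex, job position, company size, center) are also known for both arms.
- *Arm-revealing and not needed:* delivered-dose sheets for the diagnostics and follow-up consultations, the end-of-diagnostics questionnaire, and the six-month items on intervention content and component ratings.
- *Arm-revealing but possibly useful:* WAS at the end of the two-day diagnostics. Before six months it exists only in the intervention arm, so it could serve as an auxiliary variable when imputing that arm, but its presence identifies the arm.

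A file limited to the first group, with arms labelled neutrally, is therefore enough for the primary analysis.

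**The case against.** The strongest reply is that the article is open about who is unblinded and promises no masked analysis, so nothing is contradicted. It fixes a good deal: the model, the center effect, the baseline adjustment, the threshold, and one primary item at one time point. The imputation model may well be set out in an analysis plan that is not shown. The trial is sized so that a complete-case analysis keeps about its planned power, and individual data are to be shared, so others can rerun the imputation.

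Masking would also leak. The small research team receives consultation documentation every quarter, receives end-of-diagnostics questionnaires and contacts interviewees. The six-month questionnaire that carries the primary outcome also asks about intervention components, so the assistants who enter and verify it can often tell the arm.

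Most of this stands as a limit on strength. It does not supply a reason for showing arm labels to the person running the primary model, and a pre-specified imputation model would narrow the discretion without changing the sentence under Blinding.

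A reader might infer more than the documents support:

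- *That the result will be biased by some amount, such as 0.20 points.* That figure rests on an assumed shift and is not attributable to unmasking.
- *That the missing imputation detail is itself a fault.* An article commonly leaves it to the analysis plan.
- *That list generation by the principal investigator undermines concealment.* Sealed, numbered envelopes opened by the coordinator after consent address that. The role is context, not a separate error.

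**Conclusion.** The point holds as an avoidable risk of bias. The article states, rather than leaves open, that the principal investigator and analysts will know the arms, and its only reason does not apply to an analyst using a coded dataset. Nothing elsewhere in the article offsets this.

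The size of any bias cannot be estimated from the documents. What follows from the plan's own figures is exposure: about 84 of 210 primary values would be imputed, if response is 60% as assumed. That rate is a planning assumption, and an unseen analysis plan may already restrict the choices that could be influenced. Sample size and type I error rate are unaffected. Bias from self-rating by unblinded participants would remain whatever is done at analysis. The change is a worthwhile, low-cost improvement; the point does not invalidate the design.

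**What to change.** Replace the sentence on analysts under Blinding with wording such as:

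> *The imputation and primary WAS model code will be finalised, and the primary analysis run, on a dataset with neutral arm codes. It will hold only baseline and six-month variables collected in both arms, without the six-month items on intervention content and component ratings. A research assistant who does not run the analysis will hold the key. Codes will be broken once the primary output is locked; dose and end-of-diagnostics data will be merged afterwards.*

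Because the principal investigator produces the lists, the coded file should not carry the envelope numbers.

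**Cost.** One change of wording and one recoding step by existing staff. Recruitment was still under way when the article appeared, so this could be settled before analysis. The downsides should be stated in the plan:

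- Masking is imperfect. A clear effect, or the team's contact with documentation and interviews, may reveal the arms, and data entry is not masked.
- End-of-diagnostics WAS is lost as an auxiliary variable in the primary imputation. It can be used only in a sensitivity analysis after unmasking.
- Process analyses start only after the codes are broken.
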